#### Anthropometric characteristics

Height (m), weight (kg) and BMI (kg/m^2^) will be recorded using a calibrated set of scales and a stadiometer. Waist circumference and hip circumferences will be measured in centimetres using a tape measure.

#### Cardio-metabolic health

Fasting blood samples will be taken from participants and will be analysed using the Abbott Architect Ci16200 system, according to the manufacturer’s guidelines. Each sample will be assessed for a lipid standard panel (triglycerides, total cholesterol, high-density lipoprotein- HDL and non-HDL) and glucose level. Low-density lipoprotein will be determined using the Friedewald formula [28]. Blood pressure levels will be obtained using a mercury sphygmomanometer on the right arm of seated subjects.

#### Exercise capacity

The 6MWT is a commonly used objective measure of functional exercise capacity in cardiac rehabilitation [29]. The distance an individual is able to walk along a flat 25–30 m walkway over a 6 min period, with breaks as required, is recorded. The test is a self-paced, submaximal test of exercise capacity, and has been found to have a moderate-to-high reliability and validity [29].

A hospital-based exercise physiologist will perform these assessments, monitoring heart rate, oxygen saturations, the modified Borg rating of perceived exertion scale, signs and symptoms throughout. The test may be terminated by the participant or by the assessor if criteria for termination of exercise testing are met. Only one trial will be administered.

#### Health-related quality of life

The MacNew will be used for the assessment of heart disease specific health-related quality of life [30]. The MacNew is self-administered and consists of 27 items which fall into three domains (a 13-item physical limitations domain scale, a 14-item emotional function domain scale, and a 13-item social function domain scale). There are 5 items that inquire about symptoms: angina/chest pain, shortness of breath, fatigue, dizziness, and aching legs. The time frame for the MacNew is the previous two weeks, and it has good reliability and validity internationally [30].

#### Anxiety and depression

The HADS will be used for the assessment of anxiety and depression [31]. This questionnaire is a 14‐item self‐reporting questionnaire comprised of 4‐point Likert‐scaled items covering the occurrence of symptoms of anxiety (HADS‐A) and depression (HADS‐D) over the past 2 weeks. Each item on the questionnaire is scored from 0–3, so that a person can score between 0 (best outcome) and 21 (worst outcome) for either anxiety or depression.

#### Demographic and clinical questionnaire

Participants will be assessed on their socio-demographic variables (i.e. gender, age, education level, relationship status, current employment status) as well as clinical predictor variables (i.e. cardiac-related medication, other medical conditions, health care utilisation).

Eligible CR participants’ will be encouraged to adhere to the CR program, with no additional encouragement to change their physical activity and/or sedentary behaviour provided over the 12-month data collection period.

### Sample size

The G*Power software v.3.1.9.2 was used to *a priori* determine the required sample size. Previous recommendations for sample size estimation in Multiple Linear Regression problems were used [32]. With a desired effect size of f^2^ = 0.5 (large), given a maximum of 10 predictor variables including potential confounders, a sample size of *n* = 59 is needed to achieve a power of 0.95 in a test based on α = 0.05. Assuming a dropout rate of 25 %, 75 participants will be recruited for the Australian study.

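### The dropout allowance is miscalculated: 75 recruits with 25% dropout leave 56 participants, not the 59 the plan says it needs

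*Protocol article*

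**What the plan says.** The Sample size section of the protocol article describes a G*Power calculation for multiple linear regression. The inputs are a large effect, f² = 0.5, and a predictor count introduced as "given a maximum of 10 predictor variables including potential confounders". On these inputs a sample of 59 "is needed to achieve a power of 0.95 in a test based on α = 0.05". The next sentence makes the allowance for loss. It opens "Assuming a dropout rate of", gives the rate as 25%, and ends with the target: "75 participants will be recruited for the Australian study".

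The step from 59 to 75 is not shown. The article gives no other dropout rate or recruitment target.

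The Statistical analysis section says the linear regressions are to be run at every data collection point. The calculation therefore bears on the 6-week, 6-month and 12-month models as well as on baseline.

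**The concern.** An allowance for dropout is meant to leave the required number once the assumed fraction of recruits has been lost. The required number must therefore be divided by the fraction retained. A target of 75 is too low for that. It lies close to 59 × 1.25 = 73.75, which suggests that the 25% was applied to the completers instead of the recruits and the result rounded up. The article does not show this step, so the explanation is an inference, but the mismatch does not depend on it.

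At stake is whether the plan delivers, on its own assumptions, the sample and the power it states for the follow-up regressions. The Discussion relies on this when it describes the power of the sample to be recruited as adequate.

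**Working it through.** **Inputs, all from the Sample size section:** f² = 0.5; up to 10 predictors; α = 0.05; power 0.95; required n = 59; dropout 25%; recruitment target 75.

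**Step 1: reproduce the 59.** For the overall multiple-regression test (R² different from zero) with k = 10 predictors:

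- numerator degrees of freedom = k = 10
- denominator degrees of freedom = n − k − 1 = n − 11
- noncentrality λ = f² × n = 0.5n
- power = P(F′ > F critical at 0.05), where F′ is noncentral F with these parameters

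| n | denominator df | λ | power |
|---|---|---|---|
| 56 | 45 | 28.0 | 0.9360 |
| 57 | 46 | 28.5 | 0.9417 |
| 58 | 47 | 29.0 | 0.9469 |
| 59 | 48 | 29.5 | 0.9517 |
| 75 | 64 | 37.5 | 0.9905 |

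The smallest n with power of at least 0.95 is 59, as the plan states. A test of one coefficient at the same f², with 10 predictors in the model, would need only 30, so the plan sized the overall test. Because 58 already falls below 0.95, the figure of 59 has no slack to absorb a shortfall.

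**Step 2: check the dropout allowance.**

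- Recruits needed to keep 59: 59/(1 − 0.25) = 78.67, so 79. Check: 79 × 0.75 = 59.25.
- Shortfall in recruits: 79 − 75 = 4.
- Participants left from 75 at 25% loss: 75 × 0.75 = 56.25, so 56.
- Shortfall in participants retained: 59 − 56 = 3.
- Largest loss that 75 recruits can absorb: 1 − 59/75 = 0.213, or about 21%.
- Multiplying instead of dividing: 59 × 1.25 = 73.75, so 74. This is close to 75 but not equal to it.

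Rounding does not account for a gap of 4 recruits.

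**Step 3: the effect on power.** From the table, power on the plan's own test is 0.9517 at 59 and 0.9360 at 56. The difference is 0.0157, or about 1.6 percentage points.

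**The case against.** The arithmetic is not in dispute. The case on the other side is that little depends on it.

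- **The loss is small.** A fall of 1.6 points from a demanding target of 0.95 changes no design decision. This stands, and it limits the weight of the point.
- **Ten predictors is a maximum.** With 56 participants and the same test, power is 0.949 with 9 predictors and 0.960 with 8; the n needed for 0.95 is 57 and 54 respectively. So 0.936 belongs to the fullest model. This also stands, but the plan chose that model for its calculation, and 59 is the figure it states.
- **The main interest is in one exposure coefficient.** If f² = 0.5 is taken as the effect of that single coefficient, power at 56 exceeds 0.999. True on that reading, but it is a different test from the one the plan sized.
- **More than 56 rows may be analysed.** The Statistical analysis section carries the last value forward, and the Recruitment section says data from participants lost to follow-up will be used. If this covers the regressions, up to 75 rows could enter. The carry-forward sentence sits in the paragraph on the repeated measures ANOVA, so its reach is unclear, and a carried-forward value adds no new follow-up information. If such rows counted in full, no dropout allowance would be needed at all. The rule does not make 59, 25% and 75 agree.
- **Baseline is unaffected.** Correct: dropout comes later, and with all 75 available the same test has power 0.99. International pooling also concerns baseline data only, so it cannot offset losses during the Australian follow-up.

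These objections bear on how much the error matters. None of them removes it.

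**Conclusion.** The point holds. On the plan's own inputs, 75 recruits with 25% dropout leave 56 participants, 3 fewer than the stated requirement, and power on the test the plan sized is 0.936 against the stated 0.95. The size of the loss rests on f² = 0.5, all 10 predictors in the model, the overall F test at α = 0.05, and follow-up regressions based on the participants retained. With fewer predictors the loss shrinks or disappears.

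The study's feasibility is not in question. What is wrong is a printed sample size statement whose figures contradict each other. All of them stand in the same paragraph, so the mismatch does not come from condensing a longer document.

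**What to change.** Correct the last sentence of the Sample size section in one of three ways:

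1. Keep 75 and state that it allows for about 21% dropout while retaining 59.
2. Keep 75 and 25%, and state that about 56 participants would remain, with power of about 0.94 for the overall test with 10 predictors.
3. Keep 25% and set the recruitment target at 79.

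The first two cost one sentence and no extra enrolment. The third costs four more recruits. If the second is chosen, the power sentence should say that it refers to the follow-up regressions in participants retained, since baseline is not affected.

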### Statistical analysis

The number of minutes per day spent in sedentary behaviour will be calculated using standard count-based intensity threshold values of counts per minute: < 100 for sedentary behaviour (<1.5 MET). Four further summary measures of sedentary behaviours will calculated per day and averaged over valid days: (a) percentage of the wear-day spent in sedentary behaviour (b) number of sedentary bouts (defined as a period of consecutive minutes where the accelerometer registered <100 counts/minutes) (c) average duration of sedentary bouts and (d) number of sedentary breaks (defined as at least 1 min where the accelerometer registered ≥ 100 counts/minute following a sedentary bout). The Freedson Combination energy expenditure algorithm will be used to determine the intensity cut-points for MVPA. This outcome variable will be used to investigate whether participants have reached the World Health Organisation physical activity guidelines.

Linear regression models will be performed at each data collection point, where the dependent variables will be each of the health variables available. The models will have the different summary measures of sedentary behaviour (i.e. one model will be performed with each one) as main independent variables, and models will also be performed for MVPA and each of the different physical activity intensities (i.e. light, moderate and vigorous physical activity). If it is the case, quadratic trends might be explored. The models will be adjusted for total time of activity (i.e. counts per min ≥ 100), gender, socioeconomics variables, BMI and other potential confounders available.

Additional analyses will be completed with a one-way repeated measures analysis of variance (ANOVA) to test for differences in physical activity and sedentary behaviour (with a 95 % confidence interval (CI)) within the Australian sample over 12 months. Intention-to-treat analysis will be used at 6-weeks, 6 and 12-months where data is missing, bringing the last value forward. A maximum of three attempts will be made to contact participants so outcome measures can be obtained, making the analysis more complete.

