#### Sedentary behaviour and physical activity levels

Self-reported sedentary behaviour will be assessed using the PAST [21]. The PAST is a seven-item instrument that uses past-day recall of sedentary time. It asks about time spent sitting or lying (while awake) on the previous day with questions about time spent sitting or lying while at work, travelling, watching television, using the computer (excluding work), reading (excluding work), hobbies, and any other purposes not reported in the previous items. The PAST questionnaire has been found to have acceptable reliability and validity [21].

Self-reported physical activity will be assessed using the AAS [22]. The AAS has been designed to measure participation in leisure time physical activity and to assess the participant’s knowledge of current public health messages about the health benefits of physical activity. It offers a short and reliable set of questions and applies to 1 week preceding the interview, including walking for transport. The AAS has been reported as reliable and of acceptable validity [23, 24].

A triaxial commercial accelerometer (ActiGraph GT3X, Fort Walton Beach, FL) will be used to objectively assess sedentary behaviour and physical activity. Accelerometers allow an objective measurement of quantity and intensity of movement and have been found to be reliable and valid [25]. Participants will be asked to wear the monitor on their right hip during a typical week for 24 h per day for 7 consecutive days. The raw data collected by the accelerometer, counts, will be used to obtain the time spent in different physical activity intensities [26]. We will use the Freedson Combination energy expenditure algorithm to determine the intensity cut-points [27]. Sedentary behaviour will be defined as ≤ 100 counts per minute. This outcome variable will be used to investigate whether participants have reached the World Health Organisation physical activity guidelines, and to calculate sedentary time.

Both the PAST and the AAS questionnaires will be self-administered, and will be completed at the end of the 7-day accelerometer wear time to cover the same time period.

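### Sedentary minutes, bouts and breaks are analysed as daily totals, and the 12-month ANOVA has no wear-time term, so a change in waking wear between visits cannot be told from a change in behaviour

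*Protocol article*

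**What the plan says.** All of this stands in the protocol article.

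- **Sedentary time** (Statistical analysis): "The number of minutes per day spent in sedentary behaviour will be calculated using standard count-based intensity threshold values of counts per minute".
- **Further measures** (same section): "Four further summary measures of sedentary behaviours will calculated per day and averaged over valid days". They are (a) "percentage of the wear-day spent in sedentary behaviour"; (b) "number of sedentary bouts (defined as a period of consecutive minutes where the accelerometer registered" fewer than 100 counts per minute; (c) mean bout duration; and (d) "number of sedentary breaks (defined as at least 1 min where the accelerometer registered" 100 or more counts per minute after a bout.
- **Change over 12 months** (same section): a "one-way repeated measures analysis of variance (ANOVA) to test for differences in physical activity and sedentary behaviour" in the Australian sample. It is introduced as an additional analysis. The sentence does not say which sedentary or activity measure is tested.
- **Regressions at each visit** (same section): adjusted for total time at or above 100 counts per minute, gender, socioeconomic variables, BMI and other confounders that are available. Wear time is not named.
- **Wear instruction** (Sedentary behaviour and physical activity levels): participants are to "wear the monitor on their right hip during a typical week for 24 h per day for 7 consecutive days".
- **Role** (Outcome measures): accelerometer sedentary behaviour and activity are the main outcome measures. Their course over 12 months is aim (a) in the Background.

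**The concern.** A sedentary minute, bout or break can be recorded only while the monitor is worn. The plan expects wear to be incomplete despite the 24 h instruction, since it speaks of valid days and of a wear-day. Averaging over valid days equalises the number of days but not the hours worn within them.

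A one-way repeated-measures ANOVA has visit as its only factor. If participants wear the monitor for fewer waking hours at 6 or 12 months than at baseline, sedentary minutes, bouts, breaks and activity minutes can all fall without any change in behaviour, and the ANOVA attributes the fall to time. The study could then report less sitting, fewer interruptions to sitting and less activity when only compliance changed. A rise in wear would do the reverse.

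In the regressions on bouts and breaks, two people with the same rate per hour but different wear receive different exposure values. Those exposures then partly measure compliance, which may itself be related to health.

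**Working it through.** **The plan's own figures.** The protocol states no figure for wear time and none for the ANOVA. Its only calculation is the regression sample size (f² = 0.5, 10 predictors, α = 0.05, power 0.95). The omnibus F test with noncentrality f²·N gives power 0.952 at N = 59 and 0.947 at N = 58, so 59 reproduces. It does not bear on this point, except that 59 is used as the number of completers below.

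**Step 1: which quantities depend on wear.** Let W be waking wear per day, S sedentary minutes and A minutes at or above 100 counts per minute, so that S + A = W.

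| Measure | Form | Scales with W at unchanged behaviour? |
|---|---|---|
| Sedentary minutes | W × sedentary share | yes |
| (a) percentage of wear | S / W | no |
| (b) bouts per day | W × bout rate | yes |
| (c) mean bout duration | a mean, not a total | no proportional scaling |
| (d) breaks per day | W × break rate | yes |
| Light and MVPA minutes | W × activity share | yes |

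**Step 2: size per lost hour.** Change in S = 60 min × sedentary share. The shares are assumptions.

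- 60%: 60 × 0.60 = 36 min/day
- 70%: 60 × 0.70 = 42 min/day
- 80%: 60 × 0.80 = 48 min/day

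At an assumed 6 breaks per wear-hour, each lost hour removes 6 breaks/day. In relative terms, on an assumed 15 h waking base, 14 h gives 14/15 − 1 = −7%, 13.5 h gives −10% and 13 h gives −13%.

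**Step 3: what the ANOVA does with an assumed drift.** Behaviour per wear-hour was held constant over four visits, with 3000 runs per row and a 0.05 test. Every wear level, SD and drift is an assumption.

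- *Set A:* n = 59; baseline waking wear 14 h (SD 0.7 h between and 0.7 h within persons); sedentary share 70% (SD 7 points between, 4 within); 6 breaks per hour (SD 1.0 between, 0.5 within).
- *Set B:* n = 56 (75 × 0.75 = 56.25); baseline 15 h (SD 0.8 h and 0.8 h); share 68% (SD 8 and 4 points); 5 breaks per hour (SD 1.0 and 0.6).

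| Set | Fall in wear by 12 months | Rejects: minutes/day | Rejects: breaks/day | Rejects: % of wear |
|---|---|---|---|---|
| A | 0 | 5% | 5.5% | 5% |
| A | 0.25 h | 18% | 12% | 5% |
| A | 0.5 h | 60% | 39% | 5% |
| A | 1.0 h | 99.9% | 96% | 5% |
| B | 0 | 5% | 5% | 5% |
| B | 1.0 h | 99% | 67% | 4.5% |
| B | 1.5 h | 100% | 97% | 5% |

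In set A, breaks per wear-hour stayed at 5–6%. These rates are conditional on the drift put in. The percentage stays at 5% because the model makes the sedentary share independent of which hours are lost. The table shows how sensitive the ANOVA is to a given drift. It does not give the error to expect in this study.

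**Step 4: the regressions.** In the model with sedentary minutes, S and A are both present and W = S + A, so wear is already accounted for and a separate wear term would be redundant. Algebraically, b₁S + b₂A = (b₁ − b₂)S + b₂W, so the equal-wear contrast can be recovered from the fitted model. Measure (a) is divided by wear. For (b) and (d) no such identity holds: A is only one part of W, so wear is at best partly controlled.

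**The case against.** **Part of the remedy is already in the plan.** Measure (a) is wear-standardised, the ANOVA sentence names no measure, and nothing ranks minutes per day above the others. This stands. A reader might infer that the 12-month comparison is certain to be run on unstandardised totals, or that the plan ignores wear altogether. The text supports neither. It leaves the choice among the measures open, and most of them are exposed.

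**No document predicts that wear will drift.** This stands. A valid-day rule in a fuller document could also limit drift, and its absence here is not a finding. A minimum-hours rule would still not make the hours above the minimum equal across visits.

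**The proportional model does not fit 24 h wear.** This stands, and it limits both the claim and the remedy. Suppose (assumption) 8 h sleep, 10 h waking sedentary and 6 h active, with sleep not separated. Removing the monitor at night takes time below 100 counts per minute from 18 h to 10 h (−44%), leaves active minutes unchanged and barely alters daytime breaks. Percentage of wear falls from 18/24 = 75% to 10/16 = 62.5%, and breaks per wear-hour rise by about half (24/16 = 1.5). So it would be wrong to say that every total falls in proportion to wear, or that dividing by total wear removes the bias. Both statements need waking wear.

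**The regressions are largely protected.** This stands for sedentary minutes (step 4). The open-ended confounder list might admit wear time for bouts and breaks, but it does not commit to it.

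**The ANOVA is an additional analysis, and absolute MVPA minutes are needed for the WHO guideline.** Both are true. The ANOVA is nevertheless the only stated test of change in the main outcome measures. Keeping MVPA minutes for the guideline comparison does not conflict with adjusting the change analysis.

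**Conclusion.** The point holds for the 12-month ANOVA when it is run on sedentary minutes, bouts, breaks or activity minutes, and among the sedentary-measure regressions for those on bouts and breaks. For these, the plan as written cannot separate a change in waking wear from a change in behaviour.

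The size depends on a drift that the documents neither give nor predict. At assumed sedentary shares of 60–80% it is 36–48 sedentary min/day per hour of waking wear lost. Under the assumptions in set A, a fall of 0.25 h is a modest problem (18% rejection for minutes), while a fall of 1 h makes a false finding almost certain. The direction follows from the definitions of the measures, but the exact rates do not.

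The change is worth making before analysis: it concerns a main outcome measure and costs little. It is not evidence that the study's conclusions will be wrong.

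**What to change.** With sleep first separated from waking wear:

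1. Name the sedentary outcome of the 12-month comparison as percentage of waking wear (measure (a)). Alternatively, analyse sedentary, light and MVPA minutes in a repeated-measures mixed model with each visit's mean daily waking wear as a time-varying covariate.
2. Express bouts and breaks per waking wear-hour (or per sedentary hour), or add wear time as a covariate, in both the change analysis and the regressions.
3. Report mean waking wear hours per valid day at each visit.
4. Keep absolute MVPA minutes for the WHO-guideline comparison, and show daily totals descriptively.

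Without the separation of sleep, the standardised measures can be biased by night-time removal, so that step comes first.

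**Cost:** analysis-plan wording and a little more analysis work. Wear time is already needed for measure (a), so no new data are collected and the sample size does not change. Rates per hour are slightly less familiar to readers than daily totals.

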**Discussion:**

There has been limited investigation of the physical activity levels and sedentary behaviour of individuals with CHD attending CR. There are no studies assessing the relationship of these behaviours with health outcomes over the short and medium-term. As in healthy individuals, physical activity and sedentary behaviour may have independent effects on cardiovascular risk factors in people with CHD, which may contribute to recurrent cardiovascular events. If this is so, reducing sedentary behaviour may be a feasible first-line, additional and more achievable strategy to improve the health of those with CHD, alongside traditional recommendations to increase the time spent in moderate-to-vigorous intensity physical activity.

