### Outcome measures

All study measures will be collected at baseline, 6-weeks, 6 and 12 months. All assessments will be conducted at the hospital where the CR program takes place, and will be carried out by a trained health professional. This excludes the blood samples, which will be collected at pathology collection centres. The PI will ensure that all assessors comply with data collection protocols to promote data quality and minimise measurement error.

The main outcome measures are sedentary behaviour and physical activity levels objectively measured using an accelerometer. Subjective measures of sedentary behaviour (Past-Day Adults’ Sedentary Time questionnaire, PAST) and physical activity (Active Australia Survey, AAS) have also been included in this study as they are commonly employed as outcome measures in the clinical setting due to their low cost and ease of use [19]. Haskell also suggests that physical activity data is best interpreted by adopting a combination of objective and subjective measures [20]. Dependent variables include body mass index (BMI), waist-to-hip ratio (WHR), blood lipid and glucose levels, exercise capacity (6-min walk test, 6MWT), quality of life (MacNew Heart Disease Health-related Quality of Life Questionnaire, MacNew) and anxiety and depression (Hospital Anxiety and Depression Scale, HADS).

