## Discussion

Over 12 months we will assess the physical activity, sedentary behaviour levels and health outcomes of those with CHD attending a hospital-based phase II CR program. Specifically, we will measure the physical activity and sedentary behaviour levels of participants’ with CHD at the start of a phase II CR program, at the end of the program, and at 6 and 12-months to determine the short and medium-term changes in physical activity and sedentary behaviour levels. Few studies have determined whether those attending CR achieve the public health physical activity guidelines, as recommended, over the short and medium term, and no known studies have reported on CR participants’ sedentary behaviour, or sitting time. Importantly, we will also investigate the relationships between physical activity, sedentary behaviour and health outcomes at each point-in-time to determine the potential, independent risk of these behaviours, including the potential for the ACP phenomenon in CR participants.

One of the strengths of the trial is the pooling of baseline results from multiple sites, internationally. Combining data will increase the strength of statistical power analyses, with the sample size to be recruited providing adequate statistical power to detect relationships between the variables. The Australian single cohort study is prospective, allowing all the relevant information to be collected, including the objective and subjective measurement of physical activity and sedentary behaviour. The outcome measures are also collected in a ‘real-world’ situation, reflecting common practice for CR in Australia.

Limitations to the study include multiple assessors of outcome measures despite assessors remaining consistent for each outcome measure, for example, exercise capacity will always be assessed by an exercise physiologist. There is also a lack of randomisation, with recruitment of participants occurring consecutively. Other possible limitations include the potential for loss of participants to follow-up, and few participants achieving the outcome of interest, the ACP phenomenon.

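### The behaviour-health question is analysed only by same-visit regressions, so 12 months of follow-up are not used to relate behaviour to later or changing health

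*Protocol article*

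**What the plan says.** The Background sets two aims: (a) to describe physical activity and sedentary behaviour over 12 months, and (b) to assess the potential independent risk of that behaviour for cardio-metabolic health, quality of life, exercise capacity, anxiety and depression.

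Data for both aims are gathered repeatedly: "All study measures will be collected at baseline, 6-weeks, 6 and 12 months" (Outcome measures).

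For aim (b), the Statistical analysis section states: "Linear regression models will be performed at each data collection point, where the dependent variables will be each of the health variables available". Each model has one behaviour measure as its main predictor. On the sedentary side, minutes per day come first, and then "Four further summary measures of sedentary behaviours will calculated per day and averaged over valid days". On the activity side, "models will also be performed for MVPA and each of the different physical activity intensities (i.e. light, moderate and vigorous physical activity".

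The same section then plans a one-way repeated measures ANOVA over 12 months. Its variables are physical activity and sedentary behaviour only. Missing follow-up values are filled by bringing the last value forward.

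The Discussion confirms that relationships with health are examined separately at each point in time, and gives the purpose as "to determine the potential, independent risk of these behaviours, including the potential for the ACP phenomenon in CR participants". The Abstract describes the gap in the literature as follows: "There are no studies assessing the relationship of these behaviours with health outcomes over the short and medium-term".

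**The concern.** A cohort with four visits offers two things that a single survey cannot. One is the order in time: behaviour measured before the health outcome. The other is within-person change: whether a person's health moves when that person's behaviour moves. The stated regressions use neither. Each is a cross-section, and the follow-up visits serve only to repeat it.

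This bears on interpretation. Suppose, as an assumption, that people who are less well move less, or that some stable trait affects both behaviour and health. The same association would then appear at baseline, 6 weeks, 6 months and 12 months. Four concordant results could be read as four confirmations of an effect of behaviour on health, when they are one difference between people seen four times. The limitations in the Discussion do not mention this.

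**Working it through.** **1. The plan's own figure.** The article gives no count of regressions. Its one calculation is n = 59 (Sample size: f² = 0.5, 10 predictors, α = 0.05, power 0.95). The omnibus F test of one multiple regression has 10 and 59 − 11 = 48 degrees of freedom and noncentrality 0.5 x 59 = 29.5. Its power is 0.9517 at n = 59 and 0.9469 at n = 58, so 59 is reproduced. That calculation is for one regression with one observation per person, which fits the visit-by-visit reading.

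**2. Which analysis uses what.**

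| Stated analysis | Behaviour | Health outcome | Links visits |
|---|---|---|---|
| Linear regressions | yes | yes | no |
| Repeated measures ANOVA | yes | no | yes |

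No stated analysis has a yes in all three columns.

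**3. Number of models.**
- Behaviour measures (Statistical analysis): sedentary minutes + 4 further sedentary measures + MVPA, light, moderate and vigorous activity = 1 + 4 + 4 = 9.
- Health variables (Outcome measures and its subsections): BMI, waist-to-hip ratio, five lipids (triglycerides, total cholesterol, HDL, non-HDL, LDL), glucose, 6-min walk test, three MacNew domains, HADS anxiety and HADS depression = 1 + 1 + 5 + 1 + 1 + 3 + 2 = 14.
- Visits: 4.
- Total: 9 x 14 x 4 = 504, or 9 x 14 = 126 per visit.

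Other readings of the outcome list:
- one MacNew score, 12 variables: 9 x 12 x 4 = 432
- BMI dropped as an outcome because it is also a covariate, 13 variables: 468
- systolic and diastolic blood pressure added, 16 variables: 576
- a MacNew global score added as well, 17 variables: 612

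Quadratic terms are not counted.

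**4. Why agreement across visits is not replication.** Write behaviour at a visit as a stable personal level plus a within-person deviation. Let the health outcome have slope B on the first and W on the second. Leaving covariates aside, the expected same-visit slope is

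ρ x B + (1 − ρ) x W,

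where ρ is the intraclass correlation of behaviour. The documents give no ρ. Assuming 0.6 to 0.7, the between-person part carries 60 to 70% of the weight at every visit. If W = 0, so that a person's health does not follow changes in that person's behaviour, every visit still shows 0.6 B to 0.7 B. The per-visit plan cannot separate the two parts.

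**5. Interaction with carry-forward.** The planned dropout is 25% of 75, which is 0.25 x 75 = 18.75. Up to about 19 participants could therefore enter the 12-month regression with a behaviour-health pair copied from an earlier visit. In a model of change, each copy would be an artificial zero change.

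**The case against.** Several points on the other side stand.

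- **The cohort is not analysed only as cross-sections.** A reader might infer this from the regressions. The repeated measures ANOVA is a within-person analysis and serves aim (a). The Discussion also ties its short- and medium-term wording to changes in behaviour, which the ANOVA addresses. The point is limited to aim (b).
- **The wording of the aims is partly hedged.** The Abstract speaks of potential independent associations. The Discussion is open that relationships are examined at each time point, and the Abstract's sentence on missing studies describes the literature without promising a lagged analysis. What remains is that independent risk, in the Background and Discussion, is stronger than same-visit regression supports.
- **Per-visit regression has a proper use.** At baseline it suits the international study, which is cross-sectional by design.
- **A reader might turn the 504 models into a count of false positives at 0.05.** The documents do not support this. The only α stands in the sample size paragraph. A significance rule, a primary pair or a multiplicity procedure may sit in an analysis plan that is not shown. The models also overlap heavily; for example, MVPA contains moderate and vigorous activity. The count shows how often the same cross-section is repeated, and nothing more.
- **A reader might expect the mixed model to sharpen between-person slopes by using four visits.** Averaging shrinks the spread of the exposure as well as the noise in the outcome. The ratio of effective sample is (1 + 3ρx)/(1 + 3ρy), with ρx and ρy the intraclass correlations of exposure and outcome. This is 1.0 when they are equal. With each assumed to lie between 0.6 and 0.7, it runs from 2.8/3.1 = 0.90 to 3.1/2.8 = 1.11. The case for the change rests on time order and within-person change, not on precision.

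**Conclusion.** The point holds for aim (b), and it rests on a stated method, not on silence. The Statistical analysis section fixes same-visit regressions and the Discussion repeats it. About 500 models (504; plausibly 430 to 610) leave unasked whether behaviour precedes health, or changes with it.

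It would go too far to say that the study cannot answer the question. The limit lies in the stated analysis. The four visits of data would support the models needed.

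The size of any misreading cannot be computed from the documents, because they give no correlations over time. The weights of 60 to 70% above are an illustration under an assumed range. The change is worth making because it is cheap and bears directly on a stated aim.

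**What to change.** 1. For each behaviour-health pair, fit one linear mixed model over all four visits, with a random participant intercept, visit as a factor, and behaviour split into person mean and within-person deviation. Report both slopes.
2. Use observed values only in these models, without last values carried forward. This agrees with the Recruitment section, which says that data already collected from participants lost to follow-up will be used.
3. Add a lagged model of behaviour at one visit on the outcome at the next, adjusted for the outcome at the earlier visit. Same-visit deviations alone do not settle direction. The intervals between visits are unequal, so let the slope differ by interval or report it by interval. Standard errors should allow for repeated observations on a participant.
4. Keep the per-visit regressions, labelled as descriptive.
5. If steps 1 to 3 are not adopted, replace independent risk with cross-sectional association in the Background and Discussion.

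**Cost.** Plan wording and modest programming; no new data or visits. The main set becomes 126 mixed models with up to 126 lagged models beside them, against 504 per-visit models.

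**Downside.** Within-person slopes will be imprecise if behaviour changes little over 12 months. They remove only confounders that stay fixed within a person; time-varying ones remain.
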